## Abstract

**Background:**

Community-based diabetes prevention programs varied widely in effectiveness, and the intervention strategy consisting of lifestyle interventions, stepwise addition of metformin, and financial incentives has not been studied in real-world clinical practice settings. The Pre-Diabetes Interventions and Continued Tracking to Ease-out Diabetes (Pre-DICTED) trial is a pragmatic trial that aims to compare the effectiveness of a community-based stepwise diabetes prevention program with added financial incentives (intervention) versus the standard of care (control) in reducing the risk of type 2 diabetes over 3 years among overweight or obese individuals with pre-diabetes.

**Methods:**

This is an open-label, 1:1 randomized controlled trial which aims to recruit 846 adult individuals with isolated impaired fasting glucose (IFG), isolated impaired glucose tolerance (IGT), or both IFG and IGT from Singapore. Intervention arm participants attend 12 group-based sessions (2 nutrition workshops, 9 exercise sessions, and a goal-setting workshop) delivered at community sites (weeks 1 to 6), receive weekly physical activity and nutrition recommendations delivered by printed worksheets (weeks 7 to 12), and receive monthly health tips delivered by text messages (months 4 to 36). From month 6 onwards, intervention arm participants who remain at the highest risk of conversion to diabetes are prescribed metformin. Intervention arm participants are also eligible for a payment/rewards program with incentives tied to attendance at the group sessions and achievement of the weight loss target (5% of baseline weight). All participants are assessed at baseline, month 3, month 6, and every 6 months subsequently till month 36. The primary endpoint is the proportion of participants with diabetes at 3 years. Secondary endpoints include the mean change from baseline at 3 years in fasting plasma glucose, 2-hour plasma glucose, HbA1c, body weight, body mass index, physical activity, and dietary intake.

**Discussion:**

The Pre-DICTED trial will provide evidence of the effectiveness and feasibility of a community-based stepwise diabetes prevention program with added financial incentives for individuals with pre-diabetes in Singapore. The study will provide data for a future cost-effectiveness analysis, which will be used to inform policymakers of the value of a nationwide implementation of the diabetes prevention program.

**Trial registration:**

ClinicalTrials.govNCT03503942. Retrospectively registered on April 20, 2018.

**Protocol version:** 5.0 Date: 1 March 2019

**Supplementary Information:**

The online version contains supplementary material available at 10.1186/s13063-021-05500-5.

## Background

Randomized controlled trials (RCTs) have shown the effectiveness of lifestyle interventions or metformin in reducing diabetes conversion in individuals with impaired glucose tolerance (IGT) [1–3]. The Finnish Diabetes Prevention Study [1] and the US Diabetes Prevention Program (DPP) [2] both showed a relative risk reduction of 58% for lifestyle interventions, while the Da Qing IGT and Diabetes Study in China study showed a relative risk reduction of 42% [3]. The lifestyle interventions from these studies emphasized physical activity and dietary modification and included individual counseling to help participants reduce total dietary intake and improve diet quality. While the results were promising, it remains a challenge to translate these findings into real-world settings. Strategies involving multiple one-to-one patient contacts are difficult to implement and sustain on a large scale in routine healthcare settings, given competing healthcare needs and resource limitations.

Since the publication of the landmark diabetes prevention clinical trials between 1996 and 2001, a series of community-based diabetes prevention programs have been conducted [4–7]. Although these community-based programs were generally effective in preventing or delaying diabetes onset, they varied widely in effectiveness, and none matches those seen in the landmark trials [4]. One study tested the effectiveness of expert guidelines on diabetes prevention, which is lifestyle intervention with addition of metformin, when required [7]. The Diabetes Community Lifestyle Improvement Program (D-CLIP) is a randomized controlled trial in Asian Indian adults with isolated IGT, isolated impaired fasting glucose (IFG), or both IFG and IGT. The study showed that group-based lifestyle intervention plus stepwise addition of metformin led to a 32% relative risk reduction during 3 years of follow-up, compared with the standard of care [7]. A stepwise approach has the following advantages: it focuses the use of metformin to those who are likely to benefit most, i.e. those who have a suboptimal response to the lifestyle intervention and continue to show a high risk of developing diabetes. In addition, it minimizes medicalizing a pre-disease state by giving participants sufficient time to revert to normal glucose tolerance state based on lifestyle intervention alone, before introducing metformin.

Notably, with fewer resources, none of the community-based diabetes prevention programs came close to replicating the weight loss achieved in the landmark trials [8]. The steady weight regain during the study period is also a cause for concern. Weight loss appears to be the key, if not critical, intermediate outcome to reduce diabetes risk [9]. Several studies reported that weight loss is associated with the number and frequency of group sessions attended [10, 11]. In this regard, financial incentives for healthy behaviors may have a role in improving adherence and/or outcomes for participants enrolled in preventive programs [12–15]. Specifically, receipt of financial incentives was associated with higher odds of attending 9 or more DPP classes among Medicaid participants with pre-diabetes [16]. Moreover, financial incentives have been shown to improve weight loss and weight loss maintenance when combined with an evidence-based weight loss program [17–19]. The form of financial incentives may also influence the weight loss outcome. Providing a reward in the form of a lottery with a small chance of a larger payout may be more effective than fixed cash rewards, as participants tend to overestimate their chances of winning [20] and the overestimated return may serve as a stronger motivator for participants to achieve the weight loss target.

The Pre-Diabetes Interventions and Continued Tracking to Ease-out Diabetes (Pre-DICTED) program is a pragmatic randomized controlled trial with the primary objective of comparing the diabetes conversion rate at 3 years in overweight or obese men and women (body mass index (BMI) ≥ 23.0 kg/m^2^) with an elevated risk of diabetes (defined as IFG and/or IGT) between the intervention group, which receives the community-based stepwise diabetes prevention program with added financial incentives, and the control group, which receives the current standard of care. Recruitment commenced on 15 November 2017.

## Methods/Design

### Aims of study

The primary objective of this study is to evaluate the effectiveness of a community-based diabetes prevention program in reducing the diabetes conversion rate at 3 years in overweight or obese men and women (BMI ≥ 23.0 kg/m^2^) with an elevated risk of diabetes (defined as IFG and/or IGT). Secondary effectiveness objectives include the comparison of fasting plasma glucose (FPG), 2-h plasma glucose, HbA1c, weight, waist circumference, BMI, physical activity level, health status, work impairment, and diet.

### Study design

Pre-DICTED is a randomized open-label, parallel arms, controlled trial that compares a diabetes prevention program consisting of lifestyle interventions with stepwise addition of metformin and added financial incentives (intervention) versus the current standard of care (control) in overweight or obese participants with isolated IFG (FPG 6.1–6.9 mmol/L), isolated IGT (2-h plasma glucose in 75 g oral glucose tolerance test (OGTT) 7.8–11.0 mmol/L) or both IFG and IGT. The definitions of IFG and IGT are based on the criteria of the Ministry of Health in Singapore [21]. The study aims to recruit 846 participants across the two arms (423 participants per arm). The outline of the trial design is shown in Fig. 1. This clinical trial follows the guidelines for randomized clinical trials (SPIRIT checklist (Additional file 1)).

**Fig. 1 Fig1:**
[figure not shown]
Outline of trial design

### Recruitment

The study participants are referred to the Pre-DICTED program from the following sources:
Polyclinics/general practitioner clinics/hospitalsHealth Promotion Board (HPB) [22]Regional Health System Community Screening programs [23]Self-referral. A call for participants is made on HealthHub, an online portal and mobile application for Singaporeans to access health-related content and their public health records [40].

### Eligibility criteria

Inclusion criteria:
Singapore citizens or permanent residentsAge between 18 and 64 yearsBMI ≥ 23.0 kg/m^2^Laboratory tests completed within 3 months of enrolment:
FPG 6.1–6.9 mmol/L (IFG) and/or2-hour plasma glucose in 75 g OGTT 7.8–11.0 mmol/L (IGT)Willing to sign informed consent

Exclusion criteria:
Individuals with diabetes mellitusHealth conditions impeding participation in lifestyle change program (e.g., active cancer, a recent myocardial event within 6 months, heart failure, chronic kidney disease)Current pregnancy or breastfeedingIntervention with medications known to alter glucose toleranceKnown allergic reaction to metforminActive or history of lactic acidosisSevere, acute, or chronic hepatic disease

### Randomization and blinding

Participants are enrolled by study coordinators and randomized according to a 1:1 allocation ratio to the intervention and control arms using an internet-based computer program according to a randomization list. The randomization list was generated using the permuted blocks randomization technique. The block size was determined by a statistician generating the randomization list and will not be disclosed to clinical investigators and other study team members who have contact with study participants. For safety and practical reasons, participants and investigators involved in the stepwise addition of metformin are not blinded after study arm assignment. However, assessment of the primary and secondary outcomes is blinded.

### Study goals

All participants are given 2 study goals: weight loss of ≥ 5% of baseline body weight and moderate-intensity physical activity of ≥ 150 min per week. Both goals have been reported to be safe, feasible, and effective based on previous clinical trials [1, 2].

### Delivery of interventions

Participants in the intervention arm receive structured group-based lifestyle interventions with addition of metformin when needed. They are also eligible for a payment/rewards program. The participants are not allowed to participate in other clinical trials or structured programs involving lifestyle interventions during the study period.

#### Lifestyle interventions

The lifestyle intervention program is based on the Health Promotion Board’s (HPB) pre-diabetes intervention program [25], a public resource portal that includes dietary and physical activity recommendations. The lifestyle intervention program consists of (i) an intensive core intervention phase, delivered through in-person group sessions and worksheet-guided learning, and (ii) a maintenance phase, delivered through mobile phone text messages and telephone calls. Telephone delivery of lifestyle modification intervention has shown the potential to bring about weight loss in obese adults [26] and reduce diabetes incidence in men with impaired glucose tolerance [27] and has the advantage of being less resource-intensive.

##### Core intervention phase (months 1 to 3)

Weeks 1 to 6: Participants attend 12 group sessions during the first 6 weeks (twice weekly) of the program. This consists of 2 nutrition workshops (2 h per session), 9 exercise sessions (1 h per session), and in the final session a goal-setting workshop (a 2-h session) (Table 1). Group sessions are delivered at community sites in Singapore by a fixed team of facilitators that include dietitians/nutritionists and fitness instructors. The dietitians/nutritionists follow the curriculum provided by HPB and the lessons are repeated for each cohort of participants. For Chinese participants who could not understand English, Mandarin sessions are conducted simultaneously. In the group exercise sessions, fitness instructions gradually increase the exercise intensity over the 9 sessions.Weeks 7 to 12: Participants receive worksheets containing information and recommendations on physical activity and nutrition. The worksheets are distributed weekly for 6 weeks of self-directed learning at home. The participants are also given physical activity trackers and digital weighing scales to facilitate self-monitoring of physical activity and weight.

**Table 1 Tab1:** Pre-DICTED program 12-session core curriculum

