### Sample size justification

A study in the Chinese pre-diabetes population showed an 11% annual incidence of diabetes for participants who did not receive any intervention [39], which is equivalent to a 30% incidence of diabetes over 3 years. The study also showed that the relative risk (RR) for lifestyle interventions was 0.64. In addition, the Indian Diabetes Prevention Program study showed that the relative risk (RR) for lifestyle interventions and metformin was 0.72 and 0.74, respectively [5]. Risk ratios for Malays are assumed to fall between those of Indian and Chinese ethnicity. We assumed that the relative risk of converting to diabetes for those receiving intervention in multi-ethnic Singapore (composed primarily of Chinese, Malay, and Indian ethnicities) would be between the estimated effect sizes in the two cited studies; in particular, we used an RR of 0.70 for the intervention.

Given the above assumptions, we aim to recruit up to 846 participants across the two arms (423 participants per intervention arm and control arm). This will allow us to achieve 80% power with 5% two-sided type I error rate and 20% drop-out rate to detect a difference in intervention effect of 10% between the 2 study arms, assuming 33% and 23% incidence of diabetes by 3 years in the control and intervention arm respectively (RR = 0.70). The trial aims to show that the intervention is superior to the current standard of care.

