### Statistical analyses

The primary effectiveness analysis will be carried out on the modified intention-to-treat (ITT) population, consisting of all randomized participants who are present for at least one follow-up visit. The risk of prediabetes-to-diabetes conversion at 3 years will be modeled using a generalized linear model (GLM) with an identity link function and binomial variance function. Potential confounders such as age, sex, family history of diabetes and FPG at baseline will be included as covariates. The risk difference between the intervention and control groups and its 95% confidence interval will be reported. The risk of diabetes conversion at months 6, 12, 18, 24, and 30 will also be analyzed using the modified ITT set.

Sensitivity analyses will be performed on the ITT population. Multiple imputation datasets will be generated using chained equations [40], and the imputed datasets will be analyzed using the same GLM and covariates as the primary effectiveness analysis. In addition, two supportive analyses will be conducted: (i) the Kaplan-Meier estimator will be used to compare the cumulative incidence of diabetes in intervention and control participants, and (ii) the proportional hazards model for interval-censored data will be used to analyze the time to diabetes onset. The hazard ratio between the two study arms and its 95% confidence interval will be reported. The same analyses will be performed using the per-protocol population (all randomized participants who (i) have provided FPG and OGTT results at the study conclusion, and (ii) if they are in the intervention arm, have attended the goal-setting workshop, at least one nutrition workshop and at least one exercise session).

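### Only the intervention arm is treated in group cohorts, but the sample size and the stated models treat all participants as independent; if the within-cohort correlation is positive, the confidence interval is too narrow

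*Protocol article*

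**What the plan says.** Under Randomization and blinding, participants are "randomized according to a 1:1 allocation ratio to the intervention and control arms using an internet-based computer program", so the unit of randomisation is the individual.

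The core intervention phase consists of 12 group sessions over six weeks, for the intervention arm only. The article says that "Group sessions are delivered at community sites in Singapore by a fixed team of facilitators" and that, following a set curriculum, "the lessons are repeated for each cohort of participants". Under Control group, controls are counselled individually by their own primary care physician. After the six weeks, intervention contact is by worksheets done at home, text messages and telephone calls. Metformin and the weight-loss payments are decided participant by participant.

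The Sample size justification arrives at 423 per arm to "achieve 80% power with 5% two-sided type I error rate and 20% drop-out rate", for 33% against 23% with diabetes by 3 years. It mentions no cohort size, ICC or design effect.

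Under Statistical analyses, the primary risk is "modeled using a generalized linear model (GLM) with an identity link function and binomial variance function". On adjustment it says: "Potential confounders such as age, sex, family history of diabetes and FPG at baseline will be included as covariates". The imputation analyses reuse this model. The interval-censored hazards model and the generalised linear models for the secondary outcomes are described without a cohort term, random effect, frailty or robust variance.

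**The concern.** This is an individually randomised trial with group treatment in one arm, a partially nested design. Once randomised, intervention participants share peers and site delivery for 12 sessions. If that makes outcomes within a cohort more alike than outcomes between cohorts, the variance of the intervention-arm proportion is larger than the binomial formula gives. The control-arm variance is unaffected.

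A model with plain binomial variance would then report too narrow an interval for the risk difference and would reject a true null hypothesis more than 5% of the time. The same logic applies to the secondary outcomes, whose models are described in the same way. The result is intended to inform a decision on nationwide implementation, so the stated precision matters.

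**Working it through.** **Inputs from the article.** 33% (control) and 23% (intervention), two-sided 5%, 80% power, 20% drop-out, 423 per arm. **Assumed, because the article gives neither:** cohort size m = 15 to 30 and ICC = 0.005 to 0.02, in the intervention arm only.

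**1. Does 846 already contain a clustering allowance?** Take the two-proportion formula for independent participants, with mean proportion 0.28:

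n0 = [1.960·√(2·0.28·0.72) + 0.842·√(0.33·0.67 + 0.23·0.77)]² / 0.10² = 315.3, so 316 per arm.

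With continuity correction, n = (n0/4)·[1 + √(1 + 4/(n0·0.10))]² = 335 per arm. With drop-out, 335/0.80 = 418.75, so 419 per arm and 838 in total. That is within 1% of 846. Variants are 790 without the continuity correction and 856 with the correction and 23.1% (a relative risk of exactly 0.70). The stated size is reached without any design effect.

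**2. Naive precision and power.** Analysed per arm: 423·0.80 = 338.

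- Control variance: 0.33·0.67/338 = 0.000654.
- Intervention variance: 0.23·0.77/338 = 0.000524.
- Naive SE = √(0.000654 + 0.000524) = 0.0343.
- Power = Φ(0.10/0.0343 − 1.960) = 83.0% (unpooled normal approximation).

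**3. Clustering in one arm.** The design effect is DE = 1 + (m − 1)·ICC, applied to the intervention variance only.

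- True SE = √(0.000654 + 0.000524·DE).
- Power of a corrected analysis = Φ(0.10/true SE − 1.960).
- Type I error of the naive test, with equal risk in both arms = 2·[1 − Φ(1.960/√((1 + DE)/2))].
- Rejection rate of the naive test at 33% against 23% = Φ((0.10 − 1.960·naive SE)/true SE).

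| m | ICC | DE | True/naive SE | Naive type I error | Corrected power | Naive rejection rate at 33% v 23% |
|---|---|---|---|---|---|---|
| 15 | 0.005 | 1.070 | 1.015 | 5.4% | 81.8% | 82.6% |
| 15 | 0.01 | 1.140 | 1.031 | 5.8% | 80.7% | 82.3% |
| 15 | 0.02 | 1.280 | 1.060 | 6.6% | 78.4% | 81.6% |
| 20 | 0.01 | 1.190 | 1.041 | 6.1% | 79.9% | 82.0% |
| 20 | 0.02 | 1.380 | 1.081 | 7.2% | 76.9% | 81.1% |
| 30 | 0.005 | 1.145 | 1.032 | 5.8% | 80.6% | 82.2% |
| 30 | 0.01 | 1.290 | 1.063 | 6.7% | 78.3% | 81.5% |
| 30 | 0.02 | 1.580 | 1.122 | 8.4% | 73.8% | 80.2% |

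Corrected power stays at 80% or more while DE is no larger than about 1.18. At ICC = 0, DE = 1 and every figure returns to its naive value.

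**4. Number of cohorts.** 338/30 = 11.3 and 338/15 = 22.5, so about 11 to 23 cohorts at these sizes.

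**The case against.** The strongest objection is that the ICC for this endpoint may be negligible. One fixed team teaches a set curriculum to every cohort, which removes variation between facilitators as a source of clustering. Group contact fills six weeks of 36 months, and what follows is delivered to individuals. The endpoint is a laboratory glucose threshold reached at any time within 3 years. All of this stands, and it argues for the lower part of the assumed range. It does not make independence correct: peer and site effects from the shared sessions remain possible.

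A second objection is that an article leaves variance details to an analysis plan that is not shown here. In part this stands: that plan may specify a robust or partially nested analysis. But the article names the variance function of the primary model and fixes the sample size, and both are for independent participants.

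Third, not everything that cohort members have in common counts. Calendar period is shared with controls, because permuted blocks keep the arms balanced over time. Language is a characteristic from before randomisation that controls have as well. Only correlation created by the shared sessions after randomisation is one-arm clustering.

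Fourth, a reader might infer that power under the plan as written drops to 74%. It does not. The uncorrected test still rejects in 80% to 83% of trials at the design risks. The 74% belongs to a corrected analysis at the least favourable corner of the grid.

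**Conclusion.** The point holds in conditional form. The article describes group treatment in one arm, while its sample size and models are for independent participants. If the within-cohort ICC is positive, the stated interval is too narrow and the type I error is above 5%. For cohorts of 15 to 30 and an ICC of 0.005 to 0.02 in the intervention arm, with 338 analysed per arm, the true standard error is 1.5% to 12% larger than the naive one and the naive type I error is 5.4% to 8.4%. Power with a correct variance is 82% to 74%, against 83% without clustering.

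These figures rest entirely on the assumed cohort sizes and ICCs. A reader might go further and say that the standard error is probably understated by a material amount. The article does not support that, because it gives no cohort size, number of cohorts or ICC, and its design features point to a small ICC. A reader might also infer that the problem is worse for body weight and physical activity, since the sessions target them directly. That is plausible, but nothing in the article shows it.

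**What to change.** Record the assigned group-session cohort for each intervention participant. Attendance is already tied to per-session vouchers, so the records should supply it. In the primary and secondary models, use a variance that allows for clustering in the intervention arm only: either a random cohort effect in that arm, or cluster-robust standard errors with each cohort as a cluster and each control as a cluster of one. Name a small-sample correction, because ordinary robust standard errors tend to be too small with only about 11 to 23 cohorts. Report the estimated ICC and the cohort sizes.

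The cost is a cohort identifier, a short addition to the analysis text and a possibly wider interval. If the ICC is not negligible, power falls somewhat below the stated 80%. No extra participants are needed.
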